#### Missing data

Missing values (<30 %) in the APT analysis will be handled by multiple imputation techniques. It will be assumed that any missing data will occur at random and missing values will be imputed for the ITT population using multiple imputation by chained equations. The imputation models will be specified to include the individual scores observed at 8 weeks, 6 months, 1 and 2 years and any available variable that has a statistical association with the outcome to be imputed or with “missingness,” as identified in a logistic regression analysis with “missingness” as the dependent variable. Corresponding to the percentage of missing values (with a minimum of 25) datasets with imputed plausible values will obtained, with 50–100 iterations between datasets. Predictive mean matching will be employed to obtain pooled parameter estimates and their associated standard errors for all analyses.

The results of the analysis of the primary study hypothesis using the pooled results will be compared to the results obtained on the observed (PP) data alone.

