### Main study parameters/endpoints

Primary outcome measure is the difference in dislocation rate, expressed as a percentage, within the first 8 weeks between the group that receives postoperative instructions with the advice to sleep in a supine position for the first 8 weeks postoperatively and the group that receives postoperative instructions without any restriction on sleeping position. The diagnosis of a dislocated hip will be confirmed by clinical examination and X-ray findings.

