### Study procedures

After inclusion and prior to surgery, subject patients will complete the baseline questionnaire at the outpatient clinic during the intake by the nurse practitioner. The physiotherapist will mobilize patients on the day of the operation or the first postoperative day. During this mobilization patients are instructed how turn in bed and how to prevent more than 90 degrees of hip flexion and 45 degrees of rotation. The only difference in instruction between the two study arms is the sleeping position. When discharged to home or nursing home, patients receive a booklet describing the instructions relevant to the study arm they are assigned to. This booklet serves as an enchiridion for partners, physiotherapists, and other persons involved in the care of the patient. In addition, patients are handed a standardized diary booklet in which they are asked to document their sleeping position, exercise activities, experience of pain and any further comments they may want to convey. Patient will visit the outpatient clinic preoperatively and then at 8 postoperative weeks. Routine physical examination will be performed by the orthopedic surgeon. All scores and measurements will be recorded by the nurse practitioner who will also collect the diary booklet from the patients. Preoperative functional assessment will be done by pain severity (Visual Analogue Scale: range 0–10), hip function (Hip Disability and Osteoarthritis Outcome Score) and quality of life (EQ-5D). At 8 weeks follow-up the same functional assessment will be recorded by the nurse practitioner. This visit is combined with the regular postoperative control by the orthopedic surgeon. At 6, 12 and 24 months there will be follow-up questionnaires by Email, paper or telephone depending upon the availability of the patients’ Email addresses. The primary outcome: dislocations within the first 8 weeks, will be recorded in the patient’s file when visiting the emergency department.

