### Sample size calculation

The maximum allowable difference in proportion in which there is still equality in the effect is not known in the literature. Previous studies suggested “a threefold difference in dislocation rate” to be a clinically relevant difference [4]. Since the literature is suggesting an average dislocation rate of 2.03 % [8] in the posterolateral surgical approach, a dislocation percentage between 2.03 and 6.09 % is considered to be “equal.” Hence, the planned sample size is *n* = 456 THA patients. (One-sided, *α* = 0.025, *β* = 0.80, missing data 20 %).

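### The missing-data rule does not exempt dislocation status from missing-at-random imputation, although the hospital file largely supplies it; if a missed week-8 visit makes status missing, imputation overstates the rate and costs power

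*Protocol article*

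**What the plan says.** Three parts of the protocol article bear on this.

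- **Missing data.** The assumption and its scope are: "It will be assumed that any missing data will occur at random and missing values will be imputed for the ITT population". The method is multiple imputation by chained equations, used when less than 30% is missing. The section ends by applying it to the primary question: "The results of the analysis of the primary study hypothesis using the pooled results will be compared to the results obtained on the observed (PP)". Dislocation status is not set apart from the questionnaire scores.
- **Study procedures.** Events reach the data by another route: "The primary outcome: dislocations within the first 8 weeks, will be recorded in the patient’s file when visiting the emergency department".
- **Main study parameters/endpoints.** The endpoint is binary: "Primary outcome measure is the difference in dislocation rate, expressed as a percentage, within the first 8 weeks", compared between the two arms.

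Two further sections suggest that dislocation status is expected to be missing in some patients. Sample size calculation adds 20% for missing data to a calculation based on this endpoint. Populations makes absent week-8 data a ground for leaving the per-protocol set. Populations also restricts the ITT (All Patients Treated) set to randomised patients with a baseline value and one or more later measurements.

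No section says how a patient with no dislocation entry and no week-8 visit is classified.

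**The concern.** A dislocation that brings the patient to the emergency department is known whether or not the patient returns at week 8. A patient with no event who misses week 8 leaves no such trace. If that second patient is coded as missing, missingness depends on the value being imputed, which is what missing at random excludes. Covariates in the chained equations cannot remove that dependence. The observed set is then enriched for events, and imputation passes its rate on to patients who are mostly event-free.

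Only about 9 dislocations are expected in the whole trial (456 × 0.0203 = 9.3), so one or two imputed events per arm matter. With equal loss in both arms the cost is power. With unequal loss, which is possible because patients know their sleeping instructions, the estimated difference itself moves.

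**Working it through.** **Inputs.** Control rate 2.03% (Sample size calculation: "average dislocation rate of 2.03" %). Margin 6.09 − 2.03 = 4.06 points, reading the threefold criterion as a difference. One-sided α 0.025. Power 80% (printed as β = 0.80). Missing data 20%. Total 456. Assumed here: 1:1 allocation (228 per arm) and equal true rates.

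**The plan's own figure.** n per arm = (1.96 + 0.8416)² × 2 × 0.0203 × 0.9797 / 0.0406² = 189.4, so 190. Then 190 × 1.2 = 228 per arm and 456 in total, which matches.

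**Rate after imputation.** Let m be the share without week-8 data and c the share of dislocations among them that the emergency record captures. The observed fraction of an arm is d = (1 − m) + m·c·p. The rate in the observed set, which missing-at-random imputation reproduces, is r = [p(1 − m) + m·c·p] / d. With p = 0.0203, m = 0.20 and c = 1:

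- d = 0.80 + 0.20 × 0.0203 = 0.80406
- r = 0.0203 / 0.80406 = 2.52%
- excess per arm = 228 × 0.0049 ≈ 1.1 imputed dislocations, on 228 × 0.0203 ≈ 4.6 true ones

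**Power.** Wald: Φ(0.0406 / SE − 1.96), with SE = √[2r(1 − r) / (228d)].

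- Status taken from the file: SE = √(2 × 0.01989 / 228) = 0.01321, power 86.7%.
- Status truly missing at random (c = 0, 20% loss): SE = √(2 × 0.01989 / 182.4) = 0.01477, power 78.5%.
- Events captured, non-attenders imputed (c = 1, 20% loss): SE = √(2 × 0.02461 / 183.3) = 0.01639, power 69.8%.

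The total loss is 86.7 − 69.8 = 16.9 points. Of this, 8.2 (86.7 − 78.5) is ordinary information loss and 8.7 (78.5 − 69.8) comes from the wrong assumption.

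**Range over loss, full capture.**

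| Loss in each arm | Analysed rate | Power | Power if truly at random |
|---|---|---|---|
| 5% | 2.13% | 83.3% | 85.0% |
| 10% | 2.25% | 79.3% | 83.1% |
| 20% | 2.52% | 69.8% | 78.5% |
| 30% | 2.87% | 58.7% | 73.0% |

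**Range over capture, 20% loss.** With 50% capture the rate is 2.28% and power 74.0%. With 25% capture they are 2.15% and 76.2%.

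**Unequal loss, full capture (assumed splits).**

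- 10% control, 20% experimental: 2.52 − 2.25 = +0.27 points, 7% of the margin.
- 5% control, 25% experimental: +0.55 points, 14% of the margin, power about 61%.
- Swapping the arms gives the same shifts with the opposite sign, towards non-inferiority.

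**Simulation check.** 4,000 trials, 25 imputations drawn within arm, combined by Rubin's rules. Power was 70.3% with imputation and 85.4% with status from the file. At a true difference equal to the margin, one-sided error was 3.3% with complete data and 1.2% with equal 20% loss. It was 4.3% with 25% control and 5% experimental loss, and 0.7% with the reverse.

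**The case against.** **The premise is not stated.** No section says that a missed week-8 visit makes dislocation status missing. Read plainly, Study procedures makes the file the source, so no entry would mean no dislocation and little would be left to impute. The imputation details (scores at successive visits, predictive mean matching) also suit questionnaire data better. This stands as a limit: the mechanism is conditional. It does not remove the point. The rule covers any missing data, exempts nothing and reaches the primary hypothesis. If only scores were meant, the text says more than was intended and the same correction applies.

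**The numbers can be read too strongly.** A reader might infer the following, which the documents do not support:

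- *That 20% of 456, about 91 patients, would be imputed.* Patients with no later measurement are outside the ITT set, so the number is lower. The 20% is a sample-size allowance, not a week-8 loss rate, and week 8 coincides with the routine surgical visit.
- *That the whole 17-point power loss is due to the assumption.* About half is ordinary information loss.
- *That a handful of dislocations among unknown patients overturning the result shows this bias at work.* Such events would have to be unrecorded, whereas the mechanism here relies on events being recorded.
- *That loss differs widely between arms.* The article gives no loss by arm.

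**A partial check exists.** The per-protocol analysis is also primary and drops patients without week-8 data whether or not they dislocated, so this selection is largely absent there. The pooled results are to be compared with it. That helps, but the per-protocol set also excludes for poor compliance and other violations, so a discrepancy could not be traced to imputation.

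**Conclusion.** The point holds in a conditional form. As written, the rule would impute under missing at random a status that the patient's file largely supplies. If missing week-8 data are taken as missing dislocation status, the rate is overstated for any emergency capture above zero.

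The size depends on assumptions the article does not settle. With full capture and 20% loss, power falls below the planned 80%, and about 9 points of the fall are due to the assumption. With lower capture or 5% loss the effect is modest. With equal loss and equal true rates the difference is unbiased. With the assumed unequal losses it moves by roughly a quarter to half a point, in either direction. The documents do not show that imputation will in fact create dislocations, nor that the result would favour the experimental arm.

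**What to change.** Change the Missing data section in three places.

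1. Limit multiple imputation to the questionnaire scores.
2. Set dislocation status for each patient from the hospital file plus the week-8 visit or any later contact. No recorded dislocation together with a later contact counts as event-free. Most patients the present rule would impute should have such a contact, because the ITT set requires a measurement after baseline.
3. For patients still unknown, replace the missing-at-random assumption with a tipping-point table: how many dislocations among unknown experimental patients would take the upper confidence limit past the margin. This addresses unrecorded events. It is a sensitivity analysis, not evidence for the bias described above.

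The cost is a few sentences and one table; the file and the 6-, 12- and 24-month contacts already exist. The downside is that a dislocation treated elsewhere and never reported counts as none unless a later contact asks about it. For scale, at 20% loss and 50% capture, counting every unrecorded patient as event-free would give 1.83% instead of 2.03%.

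### The imputation rule does not require randomised arm, although the imputed data feed the between-arm non-inferiority test; the effect favours non-inferiority, is modest at 20–30% missing and negligible at 5%

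*Protocol article*

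**What the plan says.** The Missing data section of the protocol article states: "Missing values (<30 %) in the APT analysis will be handled by multiple imputation techniques". It then fixes the content of the imputation models: the patient's scores from each of the four follow-up times, together with "any available variable that has a statistical association with the outcome to be imputed or with" the fact of being missing, the latter identified by logistic regression. Randomised arm is not named, and nothing says that imputation is done within arm.

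The section adds: "Predictive mean matching will be employed to obtain pooled parameter estimates and their associated standard errors for all analyses". It closes by saying that the primary hypothesis will be analysed on the pooled results and "compared to the results obtained on the observed (PP) data alone".

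The Primary analysis section makes that hypothesis a between-arm non-inferiority comparison of dislocation within 8 weeks, with a three-fold difference as the limit. The Populations section restricts the per-protocol (PP) set to patients with complete measurements and no major violation, including position compliance of at least 80%.

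**The concern.** The analysis model contrasts the arms, so the imputation model must contain arm. If it does not, missing dislocations in both arms are drawn from a common model, and the imputed part of the data carries no arm difference beyond what the listed scores happen to convey. The estimated difference is pulled towards zero.

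In a superiority trial that would be conservative. In a non-inferiority trial it makes the favourable claim easier to reach.

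An association screen is a poor gatekeeper here. At 2.03% in 228 patients about 4.6 dislocations are expected in an arm, so a test of arm against dislocation has little power.

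Two further statements in the same section weaken the plan. Predictive mean matching is a way of generating imputed values; it does not pool estimates or standard errors. And the only stated check on the imputation compares two results that differ in population as well as in missing-data handling.

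**Working it through.** **Inputs from the protocol article (Sample size calculation, Missing data)**
- Test: "One-sided, *α* = 0.025". Power is taken as 80%; the article prints 0.80 as β.
- Control rate: "Since the literature is suggesting an average dislocation rate of 2.03"%.
- Limit: "a dislocation percentage between 2.03 and 6.09 % is considered to be" equal, so the absolute margin is 6.09 − 2.03 = 4.06 points.
- Allowance: "missing data 20"%. Ceiling for imputation: below 30%.
- Total of 456 patients, taken as 228 per arm.

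**Reproducing the planned size**

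n per arm = (1.960 + 0.842)² × 2 × 0.0203 × 0.9797 / 0.0406² = 189.4, rounded up to 190. Then 2 × 190 = 380 and 380 × 1.20 = 456, as printed. The absolute margin of 4.06 points is therefore the one behind the design.

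**Dilution when arm is left out of the model**

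Expected difference = (1 − missing share) × true difference. For a true 4.06 points:
- 5% missing: 0.95 × 4.06 = 3.86
- 20% missing: 0.80 × 4.06 = 3.25
- 30% missing: 0.70 × 4.06 = 2.84

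These values apply only if arm is absent in every trial. The rule does not produce that, so it has to be simulated.

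**Simulation of the rule**

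100,000 trials per scenario, 228 per arm, dislocation status missing completely at random and equally in both arms. There were 25 imputations, pooled by Rubin's rules, and non-inferiority was declared if the upper 97.5% limit (normal-approximation variance) was below 4.06 points. Arm entered the model if p < 0.05 against outcome or against missingness. The threshold is an assumption; the article gives none. The follow-up scores were not modelled.

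Share of trials in which arm is left out, 20% missing:

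| True rates | Arm left out |
|---|---|
| 2.03% vs 2.03% | 90% |
| 2.03% vs 4.06% | 76% |
| 2.03% vs 6.09% | 46% |

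Results at the limit (2.03% vs 6.09%):

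| Missing | Mean difference, arm forced in | Mean difference, rule | False non-inferiority, arm forced in | False non-inferiority, rule |
|---|---|---|---|---|
| 5% | 4.06 | 4.01 | 3.6% | 3.8% |
| 20% | 4.05 | 3.83 | 3.6% | 4.6% |
| 30% | 4.05 | 3.66 | 3.6% | 5.4% |

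A separate simulation gave 4.0% to 4.9% at 20% missing, 4.0% to 5.8% at 30%, and 3.6% to 3.8% at 5%. The increments agree.

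**Reading the two tables together**

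The mean falls by only about 0.2 points at 20% missing because the trials in which arm fails the screen are mostly those with a small observed difference. Those are also the trials that can declare non-inferiority: among trials at the limit that did so under the rule, arm had been left out in 96%. The error rate therefore rises almost as much as if arm were never included (4.6% in both cases at 20% missing).

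The 3.6% starting level exceeds 2.5% because the normal-approximation limit performs poorly with rare events. Only the rise above it belongs to the imputation rule.

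**The case against.** **The list is inclusive and the article is a condensation.** The section does not say that only these variables enter, and mandatory predictors could be set in an analysis plan that is not shown. This has some force, and arm may well be in the model in practice. But the article does more than stay silent: it states a selection rule, and a person following it would drop arm whenever the screen fails.

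**The missing share may be small.** The 20% is a general allowance and the 30% a general ceiling; neither is stated for dislocation. Dislocations are taken from the patient's file at an emergency visit, with a clinic visit at 8 weeks. The set of all patients treated also requires at least one post-baseline measurement, which removes patients with no follow-up. This stands: at 5% missing there is almost nothing to correct.

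**A reader might infer that arm is almost never in the model and that 4.06 points becomes 3.25.** The documents do not support that. Arm fails the screen about nine times in ten when the rates are equal, but then there is no difference to dilute. At the limit it enters in about half of trials, and the mean under the rule is about 3.8 points.

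**A reader might also infer that the PP comparison is useless.** It is not. PP is a co-primary population and excludes patients without 8-week data, so imputation does not dilute it. It is a partial safeguard. What it cannot do is isolate the imputation effect, because the compliance and completeness exclusions change the population at the same time.

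**The remark on predictive mean matching is about wording.** Largely so: the section already describes multiple datasets and pooled results. The sentence still names the wrong step.

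**Conclusion.** The point holds in moderated form. The stated rule can leave randomised arm out of the imputation model for a between-arm non-inferiority test, and when it does the bias favours non-inferiority. At a true three-fold difference, false non-inferiority rises by about 1 percentage point at 20% missing and about 2 at 30%, and the mean difference falls from 4.06 to about 3.8 and 3.7 points. At 5% missing or less the effect is negligible.

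These sizes rest on a 5% screening threshold, data missing completely at random in both arms, an absolute margin of 4.06 points, a normal-approximation limit, and scores that carry no arm information. If the scores are related to arm, they could restore part of the difference. The decisive unknown is the share of missing dislocation outcomes, which the article does not give. The direction of the bias does not depend on it; the size does.

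**What to change.** 1. State that randomised arm is included in every imputation model regardless of its observed association with the outcome or with missingness. The association screen can stay for the other variables.
2. State that estimates and standard errors are pooled by Rubin's rules, and describe predictive mean matching as the imputation method.
3. Compare the imputed ITT result with the observed-case ITT result, in addition to PP, so that one comparison changes only the missing-data handling.
4. Report the number of missing dislocation outcomes by arm, since this determines whether the issue matters.

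The cost is a few sentences in the analysis plan and one extra row in the results table, with no new data. A binary imputation model and a tipping-point table are optional extras. With about four or five expected events per arm at 2.03%, adding many surgeon and sleeping-position terms, or imputing separately by arm, could make the models unstable; the arm term is the essential part.

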### Statistics

#### Populations

Primary analyses will be performed for both the intention-to-treat (ITT) and per-protocol (PP) populations. The PP population of patients will comprise those who completed all measurements and did not have any reasons for exclusion from this population, including no baseline data, no data at 8 weeks and/or 6 months or major protocol violations (e.g. position compliance < 80 %).

Additional analysis will be based on an ITT (All Patients Treated) population that consists of all randomized patients who had both a baseline and at least one post-baseline measurement.

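### The imputed ITT primary result is compared with the per-protocol set as if that set were the observed data, so the comparison cannot show what imputation did

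*Protocol article*

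**What the plan says.** Three parts of the protocol article bear on this.

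- **Missing data.** Data are assumed missing at random, and "missing values will be imputed for the ITT population using multiple imputation by chained equations". The section closes by saying that the pooled result for the primary hypothesis "will be compared to the results obtained on the observed (PP) data alone". No other unimputed comparator is named.
- **Populations.** The primary analysis is planned in both ITT and PP. On the second: "The PP population of patients will comprise those who completed all measurements". Listed reasons for exclusion include absent baseline data, "no data at 8 weeks and/or 6 months or major protocol violations", with position compliance below 80% as the example of a violation. The ITT (All Patients Treated) set is "all randomized patients who had both a baseline and at least one post-baseline measurement".
- **Main study parameters/endpoints.** "Primary outcome measure is the difference in dislocation rate, expressed as a percentage, within the first 8 weeks" between the two arms. Under Study procedures, dislocations are entered in the patient's file at an emergency department visit, a route separate from the later questionnaires.

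**The concern.** The natural use of an imputed-versus-observed comparison, in a section on missing data, is to see whether the imputation moved the answer. That requires the same patients and the same allocation, with only the handling of missing values changed. Here the unimputed side is PP, which differs from ITT for reasons unrelated to a missing primary outcome.

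If the two results differ, imputation, the compliance exclusion and the loss of patients without later data are all possible causes. If they agree, these influences may have offset one another. The primary endpoint is rare (the sample size section assumes 2.03%), so a few patients moving in or out of the set can matter.

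**Working it through.** **1. The plan's own figures.** The plan gives no figure for this comparison. Its sample size supplies the scale. With both arms at 2.03%, an absolute margin of 6.09 − 2.03 = 4.06 points, one-sided α 0.025 and power 0.80 (printed as β), and assuming 1:1 allocation:

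n per arm = (1.960 + 0.842)² × 2 × 0.0203 × 0.9797 / 0.0406² = 189.4, so 190. Then 190 × 1.2 = 228 per arm, or 456 in total, as stated. The point below does not depend on this figure.

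**2. The definitions side by side.**

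| Patient | 8-week status known? | In imputed ITT? | In PP? |
|---|---|---|---|
| Complete data, compliant | yes | yes, nothing to impute for the primary outcome | yes |
| Seen at 8 weeks, no 6-month data | yes | yes, nothing to impute for the primary outcome | no |
| Complete data, position compliance below 80% | yes | yes, nothing to impute for the primary outcome | no |
| Baseline and later data, 8-week status missing | no | yes, imputed | no |

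Only the last row reflects imputation of the primary outcome. Rows two and three also separate the two analyses, and they are observed data. If completing all measurements includes the 12- and 24-month questionnaires, PP is narrower still.

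**3. Which arm loses patients.** The restricted group must sleep supine for 8 weeks, whereas the reduced-restriction group may sleep in any comfortable position. A position-compliance threshold has much to act on in the first group and little in the second. PP is therefore unlikely to be a balanced thinning of ITT.

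**4. Illustration: known outcomes left out of PP.** All rates are assumed, independent of each other and equal in both arms. Let m8 be the proportion with missing 8-week status, m6 the further proportion missing at 6 months, and c the proportion non-compliant.

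Known = 456 × (1 − m8); PP = 456 × (1 − m8) × (1 − m6) × (1 − c).

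| m8 | m6 | c | Known | PP | Known but dropped |
|---|---|---|---|---|---|
| 5% | 5% | 10% | 433 | 370 | 63 |
| 10% | 10% | 20% | 410 | 295 | 115 |
| 10% | 10% | 40% | 410 | 222 | 189 |

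**5. Illustration: the control rate moves with nothing imputed.** Assume 20% of controls are non-compliant, with r times the compliers' dislocation risk, and an overall control rate of 2.03%.

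Rate in compliers = 2.03% / (0.8 + 0.2 × r). For r = 2: 2.03 / 1.2 = 1.69%. For r = 3: 2.03 / 1.4 = 1.45%.

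**6. Illustration: the conclusion could differ with nothing imputed.** Take 456 × 0.8 / 2 = 182 known outcomes per arm and assume 4 events in each (182 × 0.0203 = 3.7 expected). Suppose PP drops 36 non-compliant controls, two of whom dislocated. Upper 95% limits for experimental minus control, against 4.06 points:

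| Data | Newcombe | Wald |
|---|---|---|
| 4/182 v 4/182 | 3.58 | 3.01 |
| 4/182 v 2/146 | 4.29 | 3.67 |

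With the Newcombe interval the two sets fall on opposite sides of the margin. With the Wald interval they do not. The article names no interval method, so this shows only what is possible.

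**The case against.** The strongest reply is that the sentence is simply the usual ITT-versus-PP comparison of a non-inferiority trial, noting in passing that PP contains no imputed values. The article does not call it a sensitivity analysis or a test of imputation, and nothing bars a further analysis. Much of this stands: PP is a proper primary population here and should stay. But even on that reading, the missing-data section labels PP as the observed data, and the definition under Populations shows that it is not.

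A second reply is that available-case and tipping-point analyses are commonly left to an analysis plan that is not shown. That is fair for any list of extra analyses, and their absence is not the point. The point is the comparator that the text does fix.

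A third reply concerns size, and it stands. The 20% allowance in the sample size need not be missing primary outcomes, since dislocations are captured through the patient's file. If few are missing, imputation changes little and the comparison is close to a plain ITT-versus-PP contrast. The non-compliance rates above are assumed. That one event shifts the risk difference by 1/182 = 0.55 points reflects rare events in any analysis and is no evidence of this fault.

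A reader might also infer that this comparison is the trial's main robustness check, or that the non-inferiority conclusion is undermined. The documents support neither. The text gives the comparison no such rank, and the primary analyses in ITT and PP are unaffected.

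**Conclusion.** The point holds as a fault in one stated rule. The comparison in the missing-data section changes the analysis population and the handling of missing values together, so its outcome cannot be attributed to imputation. This follows from the definitions alone and needs no numerical assumption.

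That the exclusion falls mainly on controls is a likely consequence of the arm-specific instructions, not a stated fact. It assumes that compliance is judged against each arm's own sleeping instruction. The Interventions section lists supine sleep among the guidelines given to all patients, but Study procedures states that sleeping position is what differs between the arms.

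The size cannot be derived from the document. The 63 to 189 dropped outcomes, the fall in the control rate to 1.69% or 1.45%, and the interval limits are illustrations under assumed rates. The endpoint, margin, sample size and the two planned primary populations are untouched.

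**What to change.** Amend the closing sentence of Missing data so that the pooled multiple-imputation ITT result is compared with an available-case ITT analysis: all randomised patients with known 8-week dislocation status, by allocated arm, without imputation. Apply the same baseline and post-baseline entry conditions to both sides, so that only the handling of missing values differs. Remove the wording that equates PP with the observed data, and keep PP as the separate primary analysis already planned under Populations. A tipping-point table for patients with unknown 8-week status is optional.

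The cost is one extra table from data already held. No change to data collection, sample size or the primary analyses is needed.
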